##### Mental health

###### Depression, Anxiety and Stress Scale

The DASS^38^ is a self-report measure made up of 21 items with three subscales that measure depression, anxiety, and stress. The DASS will also be used as a screening tool to identify eligible participants in terms of the severity of mental health symptoms. Examples of items include ‘I couldn’t seem to experience any positive feeling at all’ for the depression scale, ‘I felt I was close to panic’ for the anxiety scale and ‘I found myself getting agitated’ for the stress scale. These are then rated on a four-point Likert scale ranging from 0 (never) to 3 (almost always). Higher scores indicate higher levels of depression, anxiety and stress. The subscales have good internal reliability as measured by Cronbach’s alpha coefficients (α), which are 0.88 for depression, 0.82 for anxiety and 0.90 for stress, as well as 0.93 for the total score.^39^

###### International PA and NA schedule-short-form

The International Positive and Negative Affect Schedule-Short-Form (PANAS-SF)^40^ is a short-form version of the PANAS and uses 10 items to measure two subscales of PA and NA. Participants are asked to what extent they have felt certain states or emotions, such as ‘inspired’ for the PA scale and ‘upset’ for the NA scale. These are then rated on a five-point Likert scale ranging from 1 (very slightly or not at all) to 5 (extremely). Higher scores indicate higher levels of PA and NA. Both the PA and NA subscales have good internal reliability with both having a Cronbach’s α of 0.84.^40^

##### Psychological flexibility

###### Acceptance and Action Questionnaire-II

The Acceptance and Action Questionnaire-II (AAQ-II)^41^ is a self-report measure made up of seven items that measures psychological inflexibility or as it is also referred to, experiential avoidance. Items include a list of statements such as ‘I’m afraid of my feelings’ and ‘worries get in the way of my success’. These items are then rated on a seven-point Likert scale from 1 (never true) to 7 (always true). Scores are then totalled with higher scores indicating greater levels of psychological inflexibility and experiential avoidance. The AAQ-II has good internal reliability with a Cronbach’s α of 0.84.^41^

###### Self as Context Scale

The Self as Context Scale (SACS)^42^ uses 10 items to measure self-as-context, one of the acceptance components of psychological flexibility. Self-as-context can be described as a transcendent sense of self, where the individual is able to distance their ‘noticing self’ from internal thoughts and feelings. The SACS has two subscales: (1) centring, for example, ‘when I am upset, I am able to find a place of calm within myself’, and^1^ transcending, for example, ‘As I look back upon my life so far, I have a sense that part of me has been there for all of it’. Items are then rated on a seven-point Likert scale from 1 (strongly disagree) to 7 (strongly agree). Higher scores on the subscales indicate higher levels of centring, and transcending and a higher total score indicates greater levels of self-as-context. The SACS has good internal reliability with Cronbach’s α of 0.81 for centring, 0.78 for transcending and 0.81 for overall SACS score.^42^

##### Interoceptive awareness

###### Multidimensional Assessment of Interoceptive Awareness Version 2

The Multidimensional Assessment of Interoceptive Awareness Version 2 (MAIA-2)^43^ is a 37-item self-report measure of interoceptive awareness. The MAIA-2 uses eight subscales which are (1): noticing, for example, ‘when I am tense, I notice where the tension is located in my body’,^1^ not-distracting, for example, ‘I distract myself from sensations of discomfort’,^2^ not-worrying, for example, ‘when I feel physical pain, I become upset’,^3^ attention regulation, for example, ‘I can pay attention to my breath without being distracted by things happening around me’,^4^ emotional awareness, for example, ‘I notice how my body changes when I am angry’,^5^ self-regulation, for example, ‘when I feel overwhelmed I can find a calm place inside’,^6^ body listening, for example, ‘I listen for information from my body about my emotional state, and^7^ trusting, for example, ‘I trust my body sensations’. The items are rated on a six-point Likert scale ranging from 0 (never) to 5 (always). The scales have good internal reliability with the Cronbach’s alpha coefficients for the scales being: 0.64 for noticing, 0.74 for not-distracting, 0.67 for not-worrying, 0.83 for attention regulation, 0.79 for emotional awareness, 0.79 for self-regulation, 0.80 for body listening and 0.83 for trust.^43^

#### Physiological outcomes

These measures will provide initial data on how the intervention impacts psychophysiological factors. These measures will be collected during preintervention and postintervention and any changes analysed. The physiological measures are all being conducted in the same environment.

##### Heart rate variability

HRV will be measured using a medical-grade Holter ECG monitor. Measurements will be taken at two time points, preintervention and postintervention. Participants will lie in a supine position while the ECG monitor records for at least 5 min. Participants will be asked in advance to refrain from consuming any caffeine, alcohol, or nicotine on the day of the study, to minimise interference with the ECG. A time-domain signal measure will be calculated using the root mean square of successive interval differences (RMSSD). Frequency-domain measurements will also be calculated by using low-frequency (LF) power, high-frequency (HF) power and LF to HF ratio. This measure will be analysed in conjunction with the recent literature that suggest it is a measure of primarily the parasympathetic system.^44^

##### Interoceptive accuracy

Participants will perform a heartbeat detection task as a measure of IAc. This is conducted in the form of the heartbeat perception task which is performed according to the Mental Tracking Method^45^ using intervals of 30, 35, 40 and 45s that are separated by 30s resting periods. During each trial R–R intervals are recorded, and participants are asked to silently count their heartbeats without the use of an exteroceptive aid (such as taking one’s pulse). At the end of each period, participants verbally report the number of counted heartbeats. The participants will not be informed about the length of the counting phases nor the quality of their performance. Interoceptive sensibility will also be measured through participants’ subjective assessments about how accurately they perceived heartbeats.^46^ These measures will be completed preintervention and postintervention.

##### Blood pressure

BP will be measured at preintervention and postintervention. This will be carried out in line with the National Institute for Health and Care Excellence (NICE) recommendations. That is, BP will be collected in a room that is quiet, relaxed and temperate, while the participant will be quiet and seated, and their arm outstretched and supported, using an appropriate cuff size for the person’s arm.^47^ This outstretching of the arm will allow the practitioner to assess any undiagnosed HBP. If the participant has HBP it can make some of the osteopathic techniques less safe,^35 36^ so it is important to establish this. HBP will be determined according to the NICE recommendation of BP results that are 140/90 mm Hg and over.^47^ In addition to participant safety, measuring BP will provide data on any impact the intervention might have on this physiological indicator.

#### Additional outcomes

Demographic information will also be collected from participants relating to their gender, age and ethnic background. Although participants will have been screened for chronic pain, they will be asked whether they are currently or have recently been experiencing any neck pain or headaches. This is to inform the clinician about any problematic body areas, which may, therefore, be avoided in the intervention. The participants should be presenting as pain-free due to the initial screening process, but this is still a necessary safety measure. Participants will be excluded from the analysis if they present with neck pain or headaches.

Participants will also be asked whether they are currently receiving any mental health treatment. They will be asked whether they are currently taking any antidepressants or other related prescribed medication for mental health issues. Participants will also be asked whether they have recently attended or are currently attending any form of talking therapy or other psychotherapy. Participants’ prescription medication or psychotherapy status will not exclude them from the study. However, this will again be entered as a covariate if several participants report that they are receiving these psychological treatments.

Lastly will be the noting of any adverse events that occur during the intervention or study period. These will be filled out by the practitioner using the AERF and collected by the researcher if occurring during the intervention. If participants contact the researcher after the intervention regarding an adverse event, then this will be logged by the researcher.

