### Modifications

In the interest of participant’s safety, certain modifications may be made to the interventions if participants have body areas that are tender or if they present undiagnosed high BP (HBP). This is mostly relevant to the AVHT intervention and COMBO intervention which will have techniques that are of higher force. If a participant in the AVHT or COMBO interventions presents with HBP, neck pain or headaches during the intervention then the practitioner will not work on the cervical spine area and focus on the other spinal regions in the protocol. The justification is that HVT techniques may increase the risk of arterial damage in individuals with HBP.^35 36^

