### Participant timeline

See table 3 for the participant timeline.

**Table 3 T3:** Participant timeline

Activity/ assessment	Approx. time to complete	T_-1_ Prestudy screening/ consent	T_0_ Prestudy randomisation	T_1_ Preintervention	T_2_ Intervention	T_3_ Postintervention tests	F_1_ Follow-up 1 week
Informed consent	5 min	X					
Screening with DASS	5 min	X					
Randomisation	15 min		X				
Baseline assessment— questionnaires	15 min			X			
Baseline assessment— physiological	15 min			X			
Intervention	30 min				X		
Postintervention questionnaires	15 min					X	
Postintervention physiological	15 min					X	
Telephone interview	30 min						X

DASS, Depression Anxiety Stress Scale; F, follow-up; T, timepoint.

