#### Implementation

All participants who provide informed consent and who meet the eligibility criteria will be randomised into a study condition (as described in section Sequence generation). The randomiser [name] will not be directly involved in the recruitment or data collection, and instead, the outcome assessor will conduct the recruitment. The list of random numbers that correspond to group allocation will not be revealed to the researcher ([name]) involved in data collection or recruitment. The sealed envelopes will contain a randomisation number and corresponding intervention identity code for the allocation of participants into the intervention groups. The osteopathic practitioner will then be able to open the envelope and determine which intervention is to be delivered on the day the study is conducted.

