### Analysis of population and missing data

The study will operate on an intention-to-treat basis. All participants randomised and with preintervention data will be included in the final analysis. Any participants with missing data will be included in the analysis using the multiple imputation feature of SPSS.

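### The rule that drops participants with neck pain or headaches from the analysis contradicts the stated intention-to-treat population, and its timing relative to allocation is not fixed

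*Protocol article*

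**What the plan says.** The protocol article defines the analysed set in two places.

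- Analysis of population and missing data: "The study will operate on an intention-to-treat basis", and "All participants randomised and with preintervention data will be included in the final analysis". The only condition is having preintervention data. Missing values are to be multiply imputed.
- Additional outcomes: "Participants will be excluded from the analysis if they present with neck pain or headaches". This follows the description of a check made on top of screening: "Although participants will have been screened for chronic pain, they will be asked whether they are currently or have recently been experiencing any neck pain" (the sentence goes on to headaches). The stated purpose is to tell the clinician which body areas may need to be avoided.

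Three other places bear on timing.

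- Implementation: "All participants who provide informed consent and who meet the eligibility criteria will be randomised into a study condition". The practitioner opens the allocation envelope on the study day.
- Participant timeline, Table 3: randomisation is at "T_0_ Prestudy randomisation", ahead of the preintervention measures (T1) and the intervention (T2). The table has no row for the neck-pain and headache question.
- Modifications: if a participant in the articulation/high-velocity or combined arm "presents with HBP, neck pain or headaches during the intervention then the practitioner will not work on the cervical spine area". Treatment then continues on the other spinal regions.

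Eligibility criteria already excludes people with acute or chronic pain, on the ground that pain relief could confound the psychological outcomes.

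**The concern.** The two population rules give opposite answers for the same person, and nothing else in the article reconciles them. The analysed set is therefore undefined for anyone with a neck or head complaint, and the choice could be made after the data are seen.

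What is at stake depends on when the complaint is recorded. An exclusion based on information that precedes knowledge of allocation is independent of arm. It shrinks and unbalances small groups but does not by itself distort their comparison. An exclusion that can be triggered after allocation is known, or by the treatment itself, is no longer protected by randomisation. The Additional outcomes sentence sets no time limit, and the Modifications section describes these complaints arising during treatment in two of the four arms.

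**Working it through.** **1. The rules side by side.** Take a participant who is eligible, randomised, has preintervention data, and reports or develops a headache on the study day.

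- Analysis of population and missing data: randomised, yes; preintervention data, yes; so included.
- Additional outcomes: presents with headache; so excluded.

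Both cannot be followed.

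**2. Before or after randomisation?** Only people who meet eligibility are randomised, pain is already an eligibility exclusion, and the question is put to people already screened. On the natural reading it therefore reaches randomised participants. This is an inference, because no visit is named. The Modifications case is clearer: a complaint that appears during the session comes after allocation.

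**3. Size.** The plan has no figure to reproduce here. Inputs from the document: 32 participants (Sample size; Sequence generation) in four equal arms, 32/4 = 8 per arm. The abstract says 30, which would be 7.5 per arm; this does not affect the point. The complaint rate *p* is **assumed**, since the document gives none.

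Expected exclusions = 32*p*; mean arm size = 8(1 − *p*); standard-error ratio = 1/√(1 − *p*); chance of at least one exclusion = 1 − (1 − *p*)^32.

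| Assumed *p* | Expected exclusions | Mean arm size | SE ratio | P(at least one) |
|---|---|---|---|---|
| 5% | 1.6 | 7.6 | 1.03 | 81% |
| 10% | 3.2 | 7.2 | 1.05 | 97% |
| 20% | 6.4 | 6.4 | 1.12 | 99.9% |
| 30% | 9.6 | 5.6 | 1.20 | about 100% |

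Losses need not be even. If one arm loses 2 of 8 and the other none, the standard error of their difference rises by √(1/6 + 1/8)/√(1/8 + 1/8) − 1 = 8%. If both lose 2, it rises by 15%.

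**4. Possible bias, only if exclusion follows allocation.** Suppose one arm loses a fraction *q* whose mean change is *d* SD worse than that of those retained, and the comparison arm loses nobody. The retained mean then exceeds the full-arm mean by *q* × *d*. With 1 of 8 lost and *d* = 0.5: 0.125 × 0.5 = 0.06 SD. With 2 of 8 lost and *d* = 1.0: 0.25 × 1.0 = 0.25 SD. These shifts arise with no true difference between arms. Both *q* and *d* are assumptions.

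**The case against.** The strongest reply is that the exclusion reads as a pre-treatment check. The question is there to inform the clinician, so the answer comes before treatment. If it also comes before the envelope is opened, the exclusion is independent of arm. The Modifications section changes the treatment and says nothing about the analysis. This much stands: bias is conditional, not established. It does not remove the contradiction, and the article does not limit the exclusion to answers given before allocation is revealed.

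It can also be said that pain is a stated confounder, so leaving these people out has a rationale. That rationale supports screening before randomisation, or a sensitivity analysis. It does not make two incompatible primary populations workable.

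Some stronger readings are tempting but not supported:

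- **Detection differs by arm because Table 1 lists an examination in some arms only.** Those examinations look for somatic dysfunction or local tissue findings, not for neck pain or headache as complaints. The question is put to all participants, and clinical findings are recorded in every arm.
- **The least favourable experiences disappear.** Adverse events are logged and interviews held without restriction by arm, and nothing says the exclusion removes those records. The primary feasibility and acceptability outcomes are not shown to be affected.
- **Arms will fall below eight, or the bias is unlimited.** The first holds only if exclusions occur. The second has no support: the scenarios above give modest shifts.
- **The question is asked at T1.** Table 3 does not list it.

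**Conclusion.** The contradiction is explicit and stands on the text alone. That the exclusion acts after randomisation is the natural reading, but it is not stated.

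If only answers given before allocation is revealed count, the harm is mainly lost precision and balance: about 3 to 10 of 32 dropped and standard errors up about 5–20% at an assumed 10–30% rate. If in-session complaints count as well, the secondary between-arm comparisons can be biased, by 0.06 to 0.25 SD in the illustrated scenarios. The true rate could be lower, since people in pain are screened out, but even at 5% there is an 81% chance that at least one participant forces the question.

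This should be fixed, though it does not threaten the study. The comparisons concerned are secondary in a feasibility study that already acknowledges low power. They still matter, because the article intends the effect sizes as preliminary evidence and the results to inform a later randomised trial.

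**What to change.** Delete the sentence under Additional outcomes that excludes these participants from the analysis. Analyse all randomised participants with preintervention data in their allocated arm, as Analysis of population and missing data already says. If an analysis without them is wanted, label it a sensitivity analysis and omit only those whose complaint was recorded before allocation was revealed; this requires recording when the complaint was reported.

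The question may also be asked at screening, before randomisation. That would be in addition to the study-day safety check, which this change leaves in place. Eligibility criteria, Modifications and Additional outcomes should be reconciled on how participants with these complaints are handled; no view is taken here on their clinical management.

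The cost is one deleted sentence, optionally one added screening question and one sensitivity analysis. A few participants, some with a modified session, stay in the main analysis.

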#### Acceptability

The acceptability of the study will be largely informed by the qualitative interview following the intervention.

Participants will be interviewed about their experience of the intervention via telephone approximately 1 week after they have completed the study. The interviews will be semistructured and follow a predefined schedule (see table 2). The interview will be centred around the acceptability of the intervention, but also aspects of the study. To this end, the interview will ask questions about motivations for taking part and expectations, how informed they felt before taking part, their experience of completing the questionnaires and having physiological measures taken, and their experience of the intervention itself. Some questions will also ask participants how they have felt since the intervention. Participants will then be given a chance to provide any other feedback or thoughts on taking part in the study. The audio from the interviews will be recorded and then transcribed.

**Table 2 T2:** Interview schedule for qualitative interviews

Information and consent	1. Were there any parts of the information sheet that were difficult to understand?
	2. Did any part of your participation feel unexpected, based on what you were told in the information sheet?
Motivations for participating	3. What motivated you to participate in the study?
	4. What did you know about osteopathy before taking part?
Outcome measures—questionnaires	5. Were there any questions or words on the questionnaires that were difficult to understand?
	6. What was your experience like filling out the questionnaires?
Outcome measures—physiological	7. What was your experience of having an ECG and blood pressure taken?
	8. What was your experience of doing a heartbeat detection task?
Intervention	9. Did you feel that the practitioner adequately explained the procedures to you?
	10. What could have gone better during the session?
	11. Did you take anything useful away from the session or learn anything new?
	12. How likely are you to visit an osteopath again or seek similar treatments after this?
Closing points	13. What else could you tell us about your experience of taking part in this study?

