### Blinding (masking)

The outcome assessor will be blind to the participant’s group allocation. After preintervention psychometric and psychophysiological measures (see sections Psychological outcomes and Physiological outcomes, respectively) have been completed, the outcome assessor will leave the room (to ensure blinding) and the intervention will begin, conducted by the osteopath. Participants will not be blinded to study intervention, as the osteopathic practitioner will need to explain study and intervention procedures, in line with the osteopathic practice standards and ethical consent.^13^ The practitioner will not be blinded to the intervention type (as they need to know what intervention to deliver) but will be blinded to the study outcomes. The outcome assessor will also be conducting the data analysis, and the random numbers corresponding to each group will only be revealed when this analysis has been completed. To ensure participants do not disclose the condition they were allocated to, they will be asked not to communicate directly to the outcome assessor about the intervention they received. The study will therefore be single-blinded, where the outcome assessor is blind to intervention allocation, and the osteopathic practitioner will not be blind (hence single-blind).

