## Methods: data management and analysis

### Data management

All data will be entered electronically at the university where the data are being collected and kept in a password-protected folder, which only the outcome assessor will have access to for the duration of the study. The electronic data will be kept confidential, and participants’ names will not be linked to their datasets. For the longer term, electronic datasets will be kept indefinitely in the interest of transparency to fulfil any requests for the original data and maintained on the OSF.

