## Statistical methods

### Outcomes

Statistical analysis will be conducted using IBM SPSS (V.27). Means and SD will be reported for demographic data that includes gender, age and ethnicity. For the main analysis, data will first be examined for normality using the Shapiro-Wilk test. If data are skewed, logarithmic transformation will be used, otherwise, analysis will continue without any transformation. HRV data will be preprocessed, and inspected for any potential artefacts, and these will be removed if identified. RMSSD will be calculated on the preprocessed artefact removed data using Kubios V.3.5 (https://www.kubios.com/) via Matlab V.R2021a. IAc will then be calculated using the formula: IAc=1/4 Σ [1−(|recorded heartbeats−counted heartbeats|/recorded heartbeats)]. The psychometrics will be totalled according to the relevant questionnaire instructions and subscales.

The main analysis will comprise of seven separate mixed design two (preintervention and postintervention) by four (AVHT, STM, CST, combination (please see: Interventions section for full details of these interventions.)) analysis of covariance (ANCOVA) models. This will comprise of five separate ANCOVAs for the five psychometrics (DASS, PANAS-SF, AAQ, SACS, MAIA) and another two ANCOVAs for the physiological measures of IAc and HRV (as measured by RMSSD and LF/HF ratio). Covariates will consist of (1) whether participants are currently receiving psychotherapy (yes or no) and (2) whether participants are receiving pharmacological treatment (yes or no). Significant models will be examined further using post hoc Bonferroni tests.

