### Harms

The osteopathic practitioner will inform the participants about the general potential common adverse effects of osteopathy namely some stiffness and soreness in the days following the intervention, and rare adverse events including tissue damage,^51^ in line with informed consent processes. The osteopathic practitioner will record any adverse effects on the day the intervention is received (that occur during or immediately after the intervention) in the AERF (see online supplemental material 2). Participants will also be advised to contact the PI [name] by telephone if they have any concerns or adverse events following the intervention in subsequent days after the intervention was received. If such events are reported, these will again be reported by [name] in the AERF. Any adverse events or harms that are ranked highly on severity will be reported to the ethical committee. This includes any adverse events that, for example, require hospitalisation.

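### The blinded analysis is not protected as written: the data-access and adverse-event rules give the blinded analyst material that may reveal allocation

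*Protocol article*

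**What the plan says.** All of this is in the protocol article.

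- **Blinding (masking):** "The outcome assessor will also be conducting the data analysis, and the random numbers corresponding to each group will only be revealed when this analysis" is complete. Participants and practitioners know the treatment. After the preintervention measures the assessor leaves the room. As for participants, "they will be asked not to communicate directly to the outcome assessor about the intervention they received".
- **Data management:** all data go into a password-protected folder, "which only the outcome assessor will have access to for the duration of the study". Confidentiality and Access to data restate sole access, there for the researcher.
- **Acceptability:** "Participants will be interviewed about their experience of the intervention via telephone approximately 1 week after they have completed the study". The calls are recorded and transcribed. The interviewer is not identified.
- **Additional outcomes**, on adverse events: "These will be filled out by the practitioner using the AERF and collected by the researcher if occurring during the intervention". Later events that a participant reports to the researcher are logged by the researcher.
- **Harms:** "Participants will also be advised to contact the PI" about events in the days after treatment.
- **Table 1:** the participant's individual form records the intervention.
- **Statistical methods, Outcomes:** the HRV data are to be "inspected for any potential artefacts, and these will be removed if identified".

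**The concern.** Blinding of the assessor and analyst is the only masking of measurement and analysis in this study. It has to hold through the analysis, because that is what the protocol claims. Yet the rules on who holds the data and who handles adverse events pass records that may name or describe the technique to the person who is meant not to know it. The request to participants covers direct communication with the assessor. It does not cover recordings, transcripts or forms.

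An unblinded analyst would still have judgement to exercise, mainly over which ECG segments count as artefact. That editing feeds RMSSD and the LF/HF ratio. Self-completed questionnaires leave much less room. The study is also meant to inform a later randomised trial, so an unprotected blinding procedure could be carried forward into it.

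**Working it through.** The plan gives no figure on this point, so the check is mainly a cross-reading of roles, records and timing.

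**1. Who is the researcher?** Implementation separates the randomiser, who takes no direct part in recruitment or data collection, from the researcher involved in those tasks, and gives recruitment to the outcome assessor. Sequence generation makes the PI the randomiser. Data management gives sole access to the outcome assessor; Confidentiality and Access to data give it to the researcher. Together these identify the researcher as the assessor. Reading the word as the PI would fit Harms but sits badly with Implementation.

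**2. What reaches the assessor before the analysis ends?**

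| Record | Could it show the technique? | Rule placing it with the assessor | Rule withholding it |
|---|---|---|---|
| Interview recording and transcript | Yes: unblinded participant, talking about the session | Data management (all data) | None stated |
| Adverse-event form | Unknown: the form is in a supplement not shown | Additional outcomes | None stated; Harms sends later reports to the PI |
| Session form (Table 1) | Yes: records the intervention | Data management, if the form is entered | None stated |

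**3. When?** The interview follows that participant's postintervention tests by about a week (Table 3), so it cannot bias those measurements. It can come before the ECG editing and modelling, because the article does not say that either is finished first. An adverse-event form from the session could in principle arrive before the postintervention tests, but the handover is not timed.

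**4. How many disclosures would matter?** This is an illustration only. Inputs: 32 participants in 4 equal arms (Sequence generation), so 32/4 = 8 per arm. To fit a two-by-four model the analyst needs a group code for each participant, so one revealing record decodes its arm, and three decoded arms give the fourth. Let p be the chance that a participant's record reveals the technique. The article gives no value for p, so a range is shown. Records are assumed independent and linkable to the coded dataset.

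- Chance that an arm is identified: q = 1 − (1 − p)^8
- Chance that all four labels are decoded: P = 4q³(1 − q) + q⁴

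| p (assumed) | q | P |
|---|---|---|
| 0.05 | 0.337 | 0.11 |
| 0.10 | 0.570 | 0.42 |
| 0.20 | 0.832 | 0.87 |
| 0.30 | 0.942 | 0.98 |
| 0.50 | 0.996 | about 1.00 |

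For p = 0.10: q = 1 − 0.9^8 = 0.570, and P = 4 × 0.570³ × 0.430 + 0.570⁴ = 0.42. With interviews planned for all participants, a few revealing transcripts could be enough. The calculation concerns decoding of labels, not bias in any estimate.

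**The case against.** The strongest reply is that the documents show an unspecified data flow and nothing more. The article does not say who makes the calls or where recordings are kept, and a condensed article may leave this to the full protocol. The later access sections speak of data for analysis and of the dataset, which may mean only the quantitative files. The interview schedule never asks which technique was given. The adverse-event form is not shown and is used only when an event occurs. Trial design puts the quantitative part first. Log transformation is tied to a normality check, interoceptive accuracy has a fixed formula and multiple imputation is named, so artefact removal is the main place where judgement remains. The two adverse-event sections can also be read together: one advises whom to contact, the other says what happens if the participant contacts the researcher instead.

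Much of this stands. A reader might infer that the blinded analysis is certain to fail, or that all 32 allocations will be disclosed before analysis. The documents support neither: 32 is only a ceiling, and no breach is shown.

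The reply does not remove the contradiction. Data management opens with all data and makes no exception for interviews. The sequential design describes the order of the two parts but does not say that artefact editing and modelling end before the interviews begin, and the interviews follow each session by about a week. Even if the adverse-event sections are read together, one of them still has the researcher collect forms and log reports. The point therefore rests on rules that are stated, not on missing detail: followed literally, they expose the blinded analyst.

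**Conclusion.** The concern holds in a limited form. The claim of blinding through analysis conflicts with the sole-access rule, and the handling of adverse-event forms adds a second open route. The conclusion assumes that all data includes the interview material and that the researcher is the assessor; the first is the plain wording and the second follows from the cross-reading above.

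The size is modest. The primary outcomes, feasibility and acceptability, are largely unaffected. Many secondary outcomes are self-reported by participants who know their treatment, so analyst blinding protects them little in any case. HRV after artefact editing is the most exposed outcome. Neither the direction nor the amount of any bias can be derived from the article. The correction is cheap and worth making, because the stated safeguard could not otherwise be reported with confidence as having held.

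**What to change.** 1. Reconcile Additional outcomes with Harms, so that adverse-event forms and practitioner session forms go to the PI, who already knows the allocation. Adjust Implementation to allow this, since it keeps the randomiser out of direct data collection.
2. Amend Data management so that session forms, adverse-event forms, recordings and transcripts stay closed to the analyst until ECG artefact editing, scoring and the quantitative analysis are locked. State who conducts and holds the interviews.
3. If the assessor conducts or holds the interviews, complete and time-stamp each participant's ECG editing and scoring before that participant's interview, and restate the claim as 'assessor blind at postintervention measurement only'. That narrower claim still needs item 1, so that no form reaches the assessor before those measurements.

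Locking the analysis syntax before the first interview may no longer be possible, because Study setting gives a start date of 20 December 2022; the fix does not depend on it.

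The cost is protocol wording and a change in the order of work. Keeping the full claim means that someone other than the assessor conducts and holds the interviews, and the thematic analysis starts later. Taking item 3 avoids that but leaves a narrower blinding claim.
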